### 8.4 Follow-up of adverse events

All AEs will be followed until they have abated, or until a stable situation has been reached. Depending on the event, follow up may require additional tests or medical procedures as indicated, and/or referral to the general physician or a medical specialist.

SAEs need to be reported till end of study within the Netherlands, as defined in the protocol

### 8.5 Safety Committee

The advice(s) of the safety committee will only be sent to the sponsor of the study. Should the sponsor decide not to fully implement the advice of the safety committee, the sponsor will send the advice to the reviewing METC, including a note to substantiate why (part of) the advice of the safety committee will not be followed.

## 9. STATISTICAL ANALYSIS

In general, for differences between the effect of salbutamol in combination with placebo, and salbutamol in combination with propranolol either paired t-tests or Wilcoxon signed-rank tests will be used. Statistical analysis will be performed in close collaboration with our local Medical Statistics Department. More specific information on the statistics to be used for the different study parameters can be found below.

### 9.1 Primary study parameter

Our primary study parameter is glucose uptake by BAT, as measured by dynamic [ $^{18}\text{F}$ ]FDG PET acquisition. Patlak graphical analysis method [43] will be used to determine the fractional extraction of [ $^{18}\text{F}$ ]FDG ( $K_i$ ) in BAT

([http://www.turkupetcentre.net/petanalysis/model\\_patlak\\_interpretation.html](http://www.turkupetcentre.net/petanalysis/model_patlak_interpretation.html)). Patlak analysis will be based on the plasma input curve (time-radioactivity curve from the aorta), the BAT time-radioactivity curve, and the time in which [ $^{18}\text{F}$ ]FDG has reached steady-state in BAT (approximately 8-10 minutes). Based in the  $K_i$  we will calculate metabolic rate of glucose (MRglu).

$\text{MRglu} = (\text{Glucose concentration in plasma} / \text{Lumped constant}) * K_i$ .

(Lumped constant = 1.14 for adipose tissue)

- Differences between the effect of salbutamol in combination with placebo, and salbutamol in combination with propranolol will be assessed by paired-sample t-test or Mann-Whitney test.

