## 2. STUDY DESIGN

The study is a randomized double-blinded cross-over trial, that will be carried out at the Leiden University Medical Center (LUMC) (Figure 3). This trial encompasses one screening day, of approximately 1 hour, and two study days, both with a duration of approximately 3.5 hours.

[figure not shown]

Figure 3 The study is a randomized double-blinded cross-over trial, encompassing one screening day and two study days. IV=intravenous; PO=per oral.

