### 3.4 Sample size calculation

For this study the main outcome parameter is net glucose uptake by BAT after administration of salbutamol, as measured by dynamic  $^{18}\text{F}$ -FDG PET-CT scan.

Our sample size calculation is based on the results recently published by Blondin et al.[1] and Orava et al. [25]. Blondin et al. showed net glucose uptake by BAT as measured by dynamic  $^{18}\text{F}$ -FDG PET/CT after administration of the maximal allowable dose mirabegron (200 mg) of  $22 \pm 14$  nmol/g/min. We expect the effect of salbutamol on glucose uptake by BAT to be at least as big as the effect of the maximal allowable dose mirabegron. Orava et al. [25] showed net glucose uptake by BAT in thermoneutral condition of  $9 \pm 4$  nmol/g/min. Therefore, we predict the net glucose uptake of salbutamol in combination with propranolol to be comparable to the net glucose uptake by BAT in thermoneutral condition. Thus, we consider a difference in net glucose uptake by BAT of  $+13$  nmol/g/min after salbutamol administration as clinically relevant, with a SD of 10,  $\alpha = 0.01$ ,  $\beta = 80\%$ . Based on these parameters we need 10 subjects (<http://biomath.info/power/prt.htm>; based on Snedecor & Cochran, Statistical methods 7th edition).

In case a subject is withdrawn from the study before finishing all measurements, the investigator will try finding a replacement to maintain the initial population size.

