#### 4. TREATMENT OF SUBJECTS

This is a randomized double-blind cross-over trial in young healthy men. For all subjects the intervention consists of IV injection of salbutamol in combination with placebo and, as comparator, IV injection of salbutamol in combination with propranolol, in random order. In addition, at both study days all subjects will undergo a low-dose dynamic  $^{18}\text{F}$ -FDG PET/CT scan.

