### 9.2 Other study parameters

- Energy expenditure, as measured by indirect calorimetry
  - To compare the effect of salbutamol in combination with placebo with the effect of salbutamol in combination with propranolol paired-sample t-test or Mann-Whitney test will be performed.
- Serum markers for lipid metabolism (triglycerides (TG), total cholesterol (TC), high density lipoprotein cholesterol (HDL-C), low density lipoprotein cholesterol (LDL-C), free fatty acids)
  - To compare the effect of salbutamol in combination with placebo with the effect of salbutamol in combination with propranolol paired-sample t-test or Mann-Whitney test will be performed.
- Lipid pathway analysis (lipidomics)
  - To compare the effect of salbutamol in combination with placebo with the effect of salbutamol in combination with propranolol paired-sample t-test or Mann-Whitney test will be performed, in combination with multiple testing correction via false discovery rate estimation.

- Serum markers for glucose metabolism (glucose, insulin)
  - To compare the effect of salbutamol in combination with placebo with the effect of salbutamol in combination with propranolol paired-sample t-test or Mann-Whitney test will be performed.
- Circulating plasma BAT markers (e.g. microRNAs)
  - To compare the effect of salbutamol in combination with placebo with the effect of salbutamol in combination with propranolol paired-sample t-test or Mann-Whitney test will be performed.

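### Protocol sections 9.1 and 9.2 name the Mann-Whitney test, which is for independent samples, for paired cross-over data and so contradict section 9

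*Protocol*

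**What the plan says.** Section 2 of the protocol sets the design: "The study is a randomized double-blinded cross-over trial". Section 4 confirms that every subject receives both combinations, with "as comparator, IV injection of salbutamol in combination with propranolol, in random order".

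The opening of section 9 gives the general rule for comparing the two conditions: "either paired t-tests or Wilcoxon signed-rank tests will be used". Both are paired tests. The same paragraph then hands over to its subsections: "More specific information on the statistics to be used for the different study parameters can be found below".

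For the primary parameter, glucose uptake by BAT, section 9.1 says that the difference "will be assessed by paired-sample t-test or Mann-Whitney test". In section 9.2, each of the five parameter groups (energy expenditure, lipid markers, lipidomics, glucose markers, plasma BAT markers) carries the wording "paired-sample t-test or Mann-Whitney test will be performed". Neither subsection mentions the signed-rank test.

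Section 3.4 plans on a difference of 13 nmol/g/min, an SD of 10 and alpha 0.01 with 80% power, and concludes: "Based on these parameters we need 10 subjects".

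**The concern.** The Mann-Whitney test compares two independent samples. Used here, it would treat 10 subjects measured twice as 20 unrelated subjects in two groups of 10. Stable differences between subjects in BAT uptake, which a cross-over is meant to remove, would go back into the noise.

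The null distribution would also be wrong. For equal SDs s and within-subject correlation r, the variance of the mean difference over n pairs is 2s²(1 − r)/n. An independent-samples test works as if it were 2s²/n. With r above zero the test is too conservative and loses power. With r below zero it rejects too often.

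The conflict touches the primary endpoint. Section 9 gives way to 9.1, so an analyst who follows the protocol literally and chooses the non-parametric option would run the wrong test. For the same data, section 9 and section 9.1 name different non-parametric tests, and only one of them fits the design.

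**Working it through.** **1. Does the sample size rely on pairing?** Inputs from section 3.4: difference 13, SD 10, alpha 0.01, power 80%. Sidedness is not stated, so two-sided is assumed. The SD is read as that of the within-subject difference, which the protocol does not say.

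- Paired, normal formula: n = ((2.576 + 0.842) × 10 / 13)² = 6.9. Adding the small-sample term z²/2 = 2.576²/2 = 3.3 gives 10.2.
- Paired, exact noncentral t: n = 11, with 77.7% power at n = 10. One-sided, n = 9, with 87.3% power at n = 10.
- Unpaired, SD 10: n = 2 × (2.576 + 0.842)² × 10² / 13² = 13.8, so 14 per group.

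The stated 10 is therefore reproduced, to within one subject, only as a paired or one-sample calculation. The planned size presupposes a paired test.

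**2. What does Mann-Whitney do to 10 pairs at the planned values?** This was simulated with 20,000 trials per setting, normal data and exact null distributions for both rank tests, at two-sided alpha 0.01. The SD of the difference was held at 10 with equal SDs in the two conditions, so the SD per condition is 10/√(2(1 − r)). The correlation r is an assumption and is shown over a range.

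| r | SD per condition | Paired t, power | Signed-rank, power | Mann-Whitney, power | Mann-Whitney, true type I error (nominal 1%) |
|---|---|---|---|---|---|
| 0 | 7.07 | 78% | 74% | 85% | 1.0% |
| 0.25 | 8.16 | 78% | 74% | 72% | 0.3% |
| 0.5 | 10.0 | 78% | 74% | 49% | 0.08% |
| 0.75 | 14.14 | 78% | 74% | 14% | about 0% |
| 0.9 | 22.36 | 77% | 73% | 1% | about 0% |

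The signed-rank type I error stays at about 1% throughout. At r = −0.3 the Mann-Whitney error rises to 1.9%.

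**3. With the unequal SDs quoted in section 3.4 (14 and 4).** The SD of the difference is √(14² + 4² − 2 × r × 14 × 4) = √(212 − 112r), which equals 10 only at r = 1. The normal model and alpha are as in step 2.

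| r | SD of difference | Paired t, power | Signed-rank, power | Mann-Whitney, power |
|---|---|---|---|---|
| 0 | 14.56 | 40% | 37% | 45% |
| 0.5 | 12.49 | 55% | 51% | 46% |
| 0.75 | 11.31 | 65% | 61% | 45% |
| 1.0 | 10.0 | 78% | 74% | 46% |

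The paired tests gain as r rises. Mann-Whitney stays near 45%, because it makes no use of the pairing.

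**4. Skewed data.** With lognormal data at 22 ± 14 and 9 ± 4, r = 0.5 on the log scale and alpha 0.01, power is about 74% for Mann-Whitney and 90% for signed-rank.

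**5. At a nominal 5% and a smaller difference.** This is an illustration outside the protocol's plan, with SD 10 per condition. The Mann-Whitney type I error is about 0.9% at r = 0.5 and 0.2% at r = 0.7, against just under 5% for signed-rank. For a difference of 6.5 (half the planned 13), power is 19% against 43% at r = 0.5 and 17% against 64% at r = 0.7.

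**The case against.** The strongest reply is that this is a naming slip. Each disputed line puts Mann-Whitney beside the paired t-test, section 9 names signed-rank, and the analysis is to be done together with the local statistics department. That reading is likely right about intent. However, the name occurs six times, in exactly the subsections to which section 9 defers, so the text cannot be left to correct itself.

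Second, the protocol says only that one test or the other will be used and gives no distribution for BAT glucose uptake. If the paired t-test is used, the error has no effect. That is true, and calling Mann-Whitney the fallback is an inference. It is still offered as an acceptable primary test. A rule for choosing between the tests may properly stand in an analysis plan that is not shown, so its absence is not part of this point.

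Third, the loss depends on a correlation the protocol does not give. At r = 0 there is none, and Mann-Whitney even has slightly more power. With unequal SDs of 14 and 4 the gap at r = 0.5 is only 46% against 51%. Under the lognormal model at r = 0.5, Mann-Whitney (74 to 75%) does better than the paired t-test (67 to 68%). These limits stand. The size of the damage is uncertain, and with positive correlation the risk is a missed effect rather than a false positive. None of this makes the test valid for paired data.

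**Conclusion.** The point holds. Sections 9.1 and 9.2 name an independent-samples test for within-subject data, against section 9 and against the paired basis of the sample size.

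If Mann-Whitney were used at the planned difference of 13, SD of the difference 10 and two-sided alpha 0.01, power would fall from about 74% with signed-rank to 49% at r = 0.5 and 14% at r = 0.75, assuming normal data and equal SDs. With SDs of 14 and 4 the loss is smaller at moderate r: 5 points at r = 0.5 and 16 points at r = 0.75 (61% against 45%). A cross-over is normally chosen because positive correlation is expected, and in that range the test is conservative and wastes the design. The contradiction itself depends on none of these assumptions. Because it concerns the primary analysis, it should be corrected before any data are analysed.

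**What to change.** In section 9.1 and in each of the five places in section 9.2, replace Mann-Whitney with Wilcoxon signed-rank, so that the subsections agree with section 9. The lipidomics item keeps its false discovery rate correction.

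Signed-rank can be used at the protocol's alpha: with 10 pairs the smallest two-sided exact p-value is 2/2¹⁰ = 0.00195, below 0.01.

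The cost is wording only. Sample size, visits, measurements and burden on subjects do not change.

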### 7.2 Randomization, blinding and treatment allocation

Subjects will be randomized to decide whether they will receive salbutamol in combination with placebo on the first study day (group A), or salbutamol with the addition of propranolol (group B) (see also Figure 3, in chapter 3. 'Study design'). Randomization will be executed by the LUMC department of Clinical Pharmacology and Toxicology. In this study there will be two randomization groups (A and B) with the weight 1:1 divided over two blocks with a size of 5. We will not use stratification. The study will be performed double-blindly.

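### Section 9.1 offers a paired t-test or an unpaired Mann-Whitney test for the primary endpoint, contradicting section 9; if uptake is right-skewed and correlated within men, both options lose power that one fixed paired test would keep

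*Protocol*

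**What the plan says.** Section 9 gives a general rule for comparing the two study days: "either paired t-tests or Wilcoxon signed-rank tests will be used". Section 9.1, which is the specific section for the primary parameter, says the difference in uptake "will be assessed by paired-sample t-test or Mann-Whitney test". Section 9.2 repeats the 9.1 pairing of tests for every other parameter. No section says when the rank test replaces the t-test, and none states whether uptake is analysed raw or transformed.

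Section 9.1 defines the outcome as a product: plasma glucose divided by a lumped constant, times Ki. Section 3.4 plans on the raw scale. It takes 22 ± 14 nmol/g/min for the active condition from a mirabegron study and 9 ± 4 for the blocked condition from another study in a thermoneutral state. From a difference of 13, an SD of 10, alpha 0.01 and 80% power it concludes: "Based on these parameters we need 10 subjects".

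**The concern.** Two things look wrong. First, the protocol names two different rank tests for the same contrast, and the one in the governing section does not fit the design. Mann-Whitney treats the 20 scans as two independent groups, so the within-man comparison that justifies a cross-over of 10 men is thrown away.

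Second, the other option in 9.1, a paired t-test, is weak if it is run on raw uptake and uptake is right-skewed. The men with the largest responses then also inflate the SD of the differences. The planning figures hint at this: the mean rises 22/9 = 2.4-fold while the SD rises 14/4 = 3.5-fold.

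At stake is the power of the single primary comparison at a strict alpha. Leaving the choice of test open also lets the data make it, although that cost is small.

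**Working it through.** **1. The plan's own figure.** Standardised difference d = 13/10 = 1.3. The iterated t formula n = ((t₀.₉₉₅ + t₀.₈₀)/d)² gives 10.07, so the stated 10 reproduces. With the exact noncentral t and two-sided 0.01 (sidedness is not stated), power at n = 10 is 77.7% and 11 men are needed. One-sided, 9 suffice.

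**2. Is there a hint of skew?** The CVs are 14/22 = 0.636 and 4/9 = 0.444. A normal distribution with mean 22 and SD 14 puts Φ(−22/14) = Φ(−1.571) = 5.8% of values below zero. Section 3.4 gives no distribution, so this is only suggestive.

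**3. Lognormal margins matched to these moments.** ln-variance = ln(1 + CV²).
- Active: ln(1.405) = 0.340, ln-SD 0.583. Mean of ln = ln 22 − 0.340/2 = 2.921.
- Blocked: ln(1.198) = 0.180, ln-SD 0.425. Mean of ln = ln 9 − 0.180/2 = 2.107.
- Difference 0.814, so the geometric mean ratio is exp(0.814) = 2.26.
- The SD ratio falls from 3.5 raw to 0.583/0.425 = 1.37. The ln scale reduces the imbalance but does not remove it.
- At ln-scale correlation 0.5, the SD of the ln difference is √(0.340 + 0.180 − 2 × 0.5 × 0.583 × 0.425) = 0.522.

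**4. Power at n = 10, two-sided 0.01, correlation 0.5** (simulated; margins matched to 22 ± 14 and 9 ± 4; shape and correlation assumed):

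| Test | Named in | Lognormal | Gamma |
|---|---|---|---|
| Paired t, raw | 9 and 9.1 (scale inferred) | 0.68 | 0.58 |
| Mann-Whitney | 9.1, 9.2 | 0.74 | 0.52 |
| Wilcoxon signed-rank | 9 only | 0.90 | 0.74 |
| Paired t on ln(MRglu) | nowhere | 0.92 | 0.73 |

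Separate runs agree within about two points.

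**5. Range over the unknown correlation.** Power in %:

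| Correlation | 0 | 0.25 | 0.5 | 0.7 | 0.8 |
|---|---|---|---|---|---|
| Lognormal, raw t | 44 | 54 | 67 | 79 | 84 |
| Lognormal, signed-rank | 60 | 74 | 90 | 98 | >99 |
| Lognormal, ln t | 63 | 77 | 92 | 99 | >99 |
| Gamma, raw t | 37 | 47 | 59 | 71 | 78 |
| Gamma, ln t | 45 | 57 | 73 | 87 | 94 |
| Truncated normal, raw t | 35 | 43 | 53 | 65 | 72 |
| Truncated normal, ln t | 30 | 38 | 51 | 66 | 76 |

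Under gamma data the signed-rank test gives 0.58 / 0.75 / 0.92 at correlation 0.25 / 0.5 / 0.75, against 0.57 / 0.73 / 0.91 for ln t. Mann-Whitney falls further behind as correlation rises: at 0.75 with lognormal data it has 0.78, against 0.99 or more for both paired alternatives. With no within-man correlation there is nothing for pairing to exploit, and that disadvantage disappears.

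**6. No power to spare.** From SDs of 14 and 4, the SD of differences is √(196 + 16 − 112ρ). It equals 10 only at ρ = 1. It is 14.6 at ρ = 0 and 10.5 at ρ = 0.9, where normal-theory raw-scale power at n = 10 is 40% and 72%.

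**7. Cost of choosing after the fact.** Taking the smaller p of the t-test and the signed-rank test moves type I error from about 0.010 to 0.012.

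**The case against.** A reader might infer that the protocol commits to a raw-scale t-test, that its own figures show spread growing with the mean, and that a log-scale test is therefore required. The documents do not support that much.

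- The word raw does not appear. It is a fair inference from a target in nmol/g/min, but a rank test is also allowed.
- The two mean ± SD pairs come from different men, studies and conditions. They cannot establish a mean-variance relation within this cross-over. A paired t-test does not need equal SDs either; what matters is the shape of the differences, which is not given.
- The signed-rank test in section 9 already comes within about 3 points of ln t under lognormal data and slightly exceeds it under gamma data. The large gap is between raw t and either alternative, so it is not an advantage peculiar to logs.
- The ln test can lose. With truncated-normal data and no correlation it has 0.30 to 0.32 against 0.35 for raw t. It also changes the effect measure and fails if a Ki is not positive, which cannot be dismissed when propranolol is expected to suppress uptake almost fully.

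All of this stands, and it rules out making the ln scale mandatory.

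Two further defences are weaker. A transformation or choice rule may sit in an analysis plan that is not shown; that excuses silence, but not two sections naming different tests. Mann-Whitney may also be a slip for signed-rank. If so, the text still needs correcting, because 9.1 is the specific instruction and 9.2 repeats it.

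**Conclusion.** The point holds in a limited form. Sections 9 and 9.1 contradict each other on the rank test, and the one in 9.1 ignores the pairing. If uptake is right-skewed with a within-man correlation near 0.5, both options in 9.1 (taking the t-test on raw uptake) give up power that a fixed paired test keeps: about 16 to 24 points under lognormal data (0.68 and 0.74 against 0.90 and 0.92) and about 15 to 22 under gamma data (0.58 and 0.52 against 0.73 and 0.74). These sizes rest on assumed distributions, an assumed correlation, two-sided testing and margins borrowed from two outside studies. For near-normal uptake with low correlation the ln test gains nothing and may cost 3 to 5 points. The inflation from an open choice between tests is minor. The documents support naming one paired test; they do not settle whether it should be ln t or signed-rank.

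**What to change.** Before unblinding, name one paired primary test in section 9.1, two-sided at the planned alpha of 0.01:

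- either a paired t-test on ln(MRglu), reported as a geometric mean ratio with its confidence interval;
- or the Wilcoxon signed-rank test on the within-man differences.

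Make the other a sensitivity analysis and report the raw difference in nmol/g/min in either case. Delete Mann-Whitney from 9.1 and 9.2 so that they agree with section 9.

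The cost is a short text change, with no extra men, scans or samples. If the ln scale is chosen, the headline becomes a ratio, the +13 nmol/g/min basis in section 3.4 must be restated on that scale, and a rule for a non-positive Ki must be set in advance. Power may then be about 3 to 5 points below raw t if uptake is near-normal with low correlation. If signed-rank is chosen, at least 8 complete pairs are needed to reach 0.01: the smallest two-sided p is 2/2⁷ = 0.0156 with 7 pairs and 2/2⁸ = 0.0078 with 8. Section 3.4 plans to seek replacements for withdrawn men, so this is a remote constraint.

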### 9.2 Other study parameters

- Energy expenditure, as measured by indirect calorimetry
  - To compare the effect of salbutamol in combination with placebo with the effect of salbutamol in combination with propranolol paired-sample t-test or Mann-Whitney test will be performed.
- Serum markers for lipid metabolism (triglycerides (TG), total cholesterol (TC), high density lipoprotein cholesterol (HDL-C), low density lipoprotein cholesterol (LDL-C), free fatty acids)
  - To compare the effect of salbutamol in combination with placebo with the effect of salbutamol in combination with propranolol paired-sample t-test or Mann-Whitney test will be performed.
- Lipid pathway analysis (lipidomics)
  - To compare the effect of salbutamol in combination with placebo with the effect of salbutamol in combination with propranolol paired-sample t-test or Mann-Whitney test will be performed, in combination with multiple testing correction via false discovery rate estimation.

- Serum markers for glucose metabolism (glucose, insulin)
  - To compare the effect of salbutamol in combination with placebo with the effect of salbutamol in combination with propranolol paired-sample t-test or Mann-Whitney test will be performed.
- Circulating plasma BAT markers (e.g. microRNAs)
  - To compare the effect of salbutamol in combination with placebo with the effect of salbutamol in combination with propranolol paired-sample t-test or Mann-Whitney test will be performed.

